##### Strategies to improve adherence to interventions {11c}

Since patients are not randomized until after crural closure, surgeon bias, and technical variations of the procedure will be avoided up to this point of the operation. Anterior gastropexy will be the main study intervention that differs between the two groups. All participating surgeons are fellowship-trained, specialize in minimally invasive surgery and have received appropriate training on the procedural steps required of the protocol. This expertise and training serve to minimize technical deviations of the protocol and yield reproducible results.

##### Relevant concomitant care permitted or prohibited during the trial {11d}

The surgical technique for paraesophageal hernia repair must follow study protocol; however, the perioperative care may vary and will be left to the discretion of the surgeon. Patients are permitted to seek pre- and postoperative medical care at Cleveland Clinic Foundation (CCF) and non-CCF institutions during the trial period.

##### Provisions for post-trial care {30}

Cleveland Clinic Center for Abdominal Core Health will continue to provide post-trial care and long-term follow-up for all patients participating in the trial. If any patient suffers a complication or harm from trial participation, CCF will provide appropriate medical and surgical care as per institutional standards. Adverse events will be reported to the IRB as appropriate. No preset compensation has been arranged for those who suffer harm from the trial.

### Outcomes {12}

#### Primary outcome

The primary outcome of interest is radiographic paraesophageal hernia recurrence at 1 year postoperatively in patients receiving anterior gastropexy compared to those receiving no anterior gastropexy. An upper gastrointestinal series (UGI) or computed tomography (CT) scan will be obtained at the 1-year follow-up visit as per standard of care at our institution. Imaging obtained within the CCF system and at other institutions at the 1-year time point will be eligible for review provided that these are uploaded into Epic. Imaging will be reviewed by outcome assessors who are blinded to the treatment group and a consensus among assessors is required. A height of 2 cm of stomach, fundoplication or other abdominal organ (excluding the esophagus) above the diaphragm will constitute a radiographic recurrence, as previously described by Oelschlager et al. [25]. Herniation < 2 cm will not be considered a recurrence for the purposes of this study. Additionally, the need for reoperation secondary to fundoplication disruption, dysfunction, or slippage at any time during the study period will be considered a recurrence. We hypothesize that recurrence rates at 1 year after surgery for patients who receive anterior gastropexy will be decreased by 15% or more compared to those receiving no anterior gastropexy.

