##### Criteria for discontinuing or modifying allocated interventions {11b}

If at any point during the operation, the surgeon believes inclusion in the study is not in the patient’s best interest, the surgeon may choose to withdraw the patient from the study and complete the operation per his or her standard of care. However, if the patient is included in the study, there will be no deviation from the study protocol and surgeons must perform the key operative steps and technique for anterior gastropexy per the established study protocol. In the event of an immediate recurrence or other postoperative complication, if a gastropexy is added during a subsequent operation, the patient will be included in the intent-to-treat analysis.

As with any surgical procedure, patients may experience pain, bleeding, and discomfort. There is also a small risk of seroma, hematoma, inflammation, wound dehiscence, and infection at the surgical sites. After PEHR, there is a possibility of other symptoms including visceral injury, leak, nausea, vomiting, abdominal distention, dysphagia, odynophagia, GERD, and recurrent hiatal hernia. Patients in both study arms will receive appropriate clinical management for these symptoms at the discretion of the treating surgeon. If at any point during the postoperative period the surgeon believes gastropexy takedown or local suture removal is required to treat an ongoing symptom and/or is in the patient’s best interest, this may be performed at the surgeon’s discretion and will be documented.

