### Sample size {14}

Assuming a 20% rate of loss to follow-up, enrollment of 240 participants with 120 participants in each arm will provide at least 80% power for showing superiority of anterior gastropexy to no anterior gastropexy for the primary endpoint of decreased recurrence rates by 15% at the 1-year postoperative visit using a two-sided chi-square test and an alpha level of 5%. For the purpose of calculating the power of this study, the proportion of recurrences in the control group (no anterior gastropexy) is estimated to be 0.24. This is based on the reported recurrence rates for paraesophageal hernia repair without gastropexy, ranging from 7 to 66% [3, 16, 21–24], with the majority falling between 13 and 42% [3, 16, 23, 24] at various time points after surgery.

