Anterior gastropexy, along with several other technical steps, serve as branch points during operative decision-making which may affect outcomes of PEHR. These include, but are not limited to the following: minimally invasive versus open approaches, various crural closure techniques, addition or avoidance of fundoplication, mesh use versus no mesh use, and the use or avoidance of anterior gastropexy. We chose to exclude patients with mesh at the hiatus because there is evidence that it, at most, delays early recurrence of paraesophageal hernias [2, 25]. Our primary endpoint of PEH recurrence at 1 year ± 6 months is a short to medium-term follow-up period, and mesh placement would likely be a confounder if included. Patients not eligible for a minimally invasive repair were similarly excluded since there is evidence, albeit retrospective in nature, that open PEH repair has lower recurrence rates compared to laparoscopic approaches [24, 29]. On the other hand, there is no evidence to suggest that a fundoplication affects recurrence rates after paraesophageal hernia repair [30, 31]. Therefore, fundoplications were allowed in this protocol per surgeon discretion and are not expected to confound the primary endpoint. We will analyze this assumption at the conclusion of the study with a multivariate logistic regression model in patients with and without a fundoplication. We also hypothesize that a recurrent hiatal hernia with a fundoplication in the mediastinum is more symptomatic than recurrences without a fundoplication in the mediastinum. A priori exploratory outcome analyses will be performed to examine this hypothesis. Since there is no evidence to show that a fundoplication decreases recurrence rates, and it has the potential for increased symptoms of dysphagia, regurgitation, and chest pain after recurrence, it is currently not our standard practice to routinely perform a fundoplication during paraesophageal hernia repair. This study will elucidate these hypotheses and help power a larger study for a more formal evaluation. Patients who have undergone a prior paraesophageal hernia repair, cruroplasty, or anti-reflux procedure or have had esophageal or gastric resections in the past were excluded due to the inability to control for the variable anatomy at the hiatus which could confound resultant effects on recurrence rates and patient-reported symptoms. For similar reasons, if a Collis gastroplasty is needed for a shortened esophagus, these patients are not randomized. Our group rarely performs this procedure and if needed, the anatomic variation in this scenario would not be representative of the standard patient in this study population.

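### The primary endpoint counts reoperation only for fundoplication failure, so a hernia re-repaired before an eligible scan in a patient without a fundoplication has no route to being scored a recurrence

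*Protocol article*

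**What the plan says.** In the protocol article, Outcomes {12}, Primary outcome, there are two ways to become a recurrence.

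- **Imaging.** At least 2 cm of stomach, fundoplication or another abdominal organ lies above the diaphragm; less than 2 cm does not count. On timing: "Imaging obtained within the CCF system and at other institutions at the 1-year time point will be eligible for review". Section {18b} sets the 1-year window at 6 to 18 months, and Table 1 schedules the recurrence assessment at the 1-year visit only.
- **Reoperation.** "the need for reoperation secondary to fundoplication disruption, dysfunction, or slippage at any time during the study period will be considered a recurrence".

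Three other places bear on this:

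- Section {11b} foresees an early failure: "In the event of an immediate recurrence or other postoperative complication, if a gastropexy is added during a subsequent operation", the patient stays in the intent-to-treat analysis. It does not say how that patient's endpoint is scored.
- Section {20c} scores patients lost to follow-up as having no recurrence and keeps 240 as the denominator.
- Fundoplication is left to the surgeon (Eligibility criteria {10}), and the Discussion states that "it is currently not our standard practice to routinely perform a fundoplication during paraesophageal hernia repair".

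**The concern.** The reoperation rule shows that the authors want some reoperations to settle the endpoint whatever a later scan shows. The rule names only fundoplication causes and omits the event that the endpoint is named after, a recurrent hernia that needs a second repair. Patients without a fundoplication, the usual case at this centre, cannot meet it.

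Two misclassifications follow. A clear surgical failure can end up without the endpoint. In a control patient, the deciding scan may even be taken after a gastropexy was added at the second operation. In the other direction, a reoperation for fundoplication dysfunction without any herniation enters an endpoint defined as radiographic herniation of at least 2 cm.

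This is the only primary endpoint, and about 29 events are expected among 120 controls (0.24 × 120 = 28.8), so a few misclassified patients matter. If gastropexy prevents recurrence, re-repairs are expected more often in controls, so losing them biases the difference towards zero.

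**Working it through.** **Step 1: apply the rules to four patients (months are illustrative).**

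| Patient | Imaging route | Reoperation route | Result |
|---|---|---|---|
| No fundoplication; hernia recurs, re-repaired at month 3; intact at month 12 | Early scan is outside 6–18 months; later scan shows the second repair | Not available | No route to recurrence |
| No fundoplication; scan at month 8 shows ≥ 2 cm; re-repaired at month 9 | Scan is in the window and could count | Not available | Can be a recurrence |
| Fundoplication slipped, with herniation; reoperated | Depends on the scan date | Available | Recurrence |
| Fundoplication dysfunction, no herniation; reoperated | Not met | Available | Recurrence |

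The gap is the first row: re-repair before 6 months, or without an eligible scan, in a patient without a fundoplication. The fourth row is the reverse error.

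**Step 2: reproduce the planned sample size.** Inputs from Sample size {14}: "the proportion of recurrences in the control group (no anterior gastropexy) is estimated to be 0.24"; the effect is the "primary endpoint of decreased recurrence rates by 15% at the 1-year postoperative visit"; two-sided alpha 5%; 20% loss; 120 per arm; and the claim that this "will provide at least 80% power". I read the 15% as percentage points (0.24 vs 0.09), because a relative 15% reduction (0.24 vs 0.204) would give power of only about 9% at 96 per arm.

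n per arm = [1.960·√(2·0.165·0.835) + 0.842·√(0.24·0.76 + 0.09·0.91)]² / 0.15² = (1.029 + 0.433)² / 0.0225 ≈ 94.9, so 95.

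95 / 0.8 = 118.75, so 119 per arm, or 238 against the 240 stated. The stated figure reproduces. With 120 × 0.8 = 96 evaluable per arm, power is 80.4% by the normal approximation. It is 81.8% exactly, summing binomial probabilities over all tables where the uncorrected chi-square exceeds 3.84.

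**Step 3: illustrate the loss.** Let k control re-repairs be scored as no recurrence, so the control rate becomes 0.24 − k/96. Two assumptions bracket the gastropexy arm:

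- *Proportional loss:* the same share of recurrences is lost in each arm, so its rate is 0.09 × (0.24 − k/96)/0.24.
- *Controls only:* it stays at 0.09. This is the worst case.

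| k | Control rate | Proportional: other arm, difference, exact power | Controls only: difference, exact power |
|---|---|---|---|
| 0 | 0.240 | 0.090, 15.0 points, 81.8% | 15.0 points, 81.8% |
| 2 | 0.219 | 0.082, 13.7 points, 77.4% | 12.9 points, 71.2% |
| 4 | 0.198 | 0.074, 12.4 points, 72.5% | 10.8 points, 58.0% |

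The power calculation uses 96 completers per arm. On the denominator that {20c} plans for the analysis, each misclassified patient is 1/120 = 0.83 points.

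**Step 4: how many patients?** The Background {6a} cites revisional surgery for recurrent hernia in 0.01 to 7% of patients, without a rate at 6 months or 1 year. At the lower end the effect is nil.

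**Step 5: the reverse error.** If hernia-free fundoplication reoperations added 1 point to both arms (an assumption), normal-approximation power would move from 80.4% to 78.5%; 3 points would give 75.0%.

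**The case against.** The strongest reply is that the protocol is silent here, and silence is not a rule. Section {20c} applies no recurrence to patients lost to follow-up, and a reoperated patient is not lost; {11b} itself calls the event a recurrence. That stands as far as the wording goes: no sentence scores this patient as a non-recurrence. But only two routes are defined, and this patient meets neither.

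Several stronger readings are tempting and not supported:

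- *That every re-repaired hernia is lost.* A scan within 6 to 18 months but before the reoperation could qualify, and slippage or disruption may capture herniation in patients with a fundoplication.
- *That 7 of the 15 points could go.* This takes the top of a range with no stated 1-year rate. It also puts all the re-repairs in controls, before any eligible scan and outside the fundoplication clause. Even at 7%, proportional loss gives 0.170 vs 0.064, a difference of 10.6 points, so 4.4 points are lost.
- *That the unblinded surgeon can steer the endpoint by choosing a fundoplication after allocation.* The order of steps in {11a} permits a later choice, but no passage says when it is made, and fundoplication is a covariate in the primary model.
- *That fundoplication reoperation must leave the endpoint.* A prespecified composite is a legitimate choice; removing it is partly preference.

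**Conclusion.** The point holds as a defect in the stated endpoint definition. Followed literally, it gives no route to recurrence for a hernia re-repaired before an eligible scan in a patient without a fundoplication, a course of events that {11b} foresees. It also counts fundoplication failures in which nothing has herniated. The sample size itself is sound.

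The direction of the first error, towards no difference, rests on gastropexy being effective and on re-repairs following recurrences. The size is uncertain and probably small. Two such control patients would cost between about 4 and 11 points of power (81.8% to 77.4% or 71.2%), and four between about 9 and 24 (to 72.5% or 58.0%), depending on whether the gastropexy arm loses events too. These are illustrations under assumed counts, not forecasts.

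**What to change.** Reconcile Primary outcome {12}, {11b} and {20c} before analysis.

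1. Add to the primary endpoint reoperation for recurrent hernia, or herniation of at least 2 cm documented before the 1-year image, at any time in the study period and with or without a fundoplication.
2. State that such a patient remains a recurrence whatever later imaging shows and whether or not a 1-year image exists, including when a gastropexy was added at the second operation.
3. Have the assessors adjudicate these cases blinded to arm, from pre-reoperation imaging where it exists.
4. Report a sensitivity analysis that excludes fundoplication reoperations without herniation of at least 2 cm.

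The cost is a wording change and a review of the few reoperated patients' records. Neither the sample size nor patient care changes. The downside is that a few events will rest on unscheduled imaging, or on the operative findings of a surgeon who knows the allocation, and blinded review does not fully remove that.

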#### Secondary outcomes

Patient-reported GERD, dysphagia, odynophagia, gas bloat symptoms, and patient satisfaction in the 30-day postoperative period and at 1-year follow-up will be measured by the GERD-Health-related Quality of Life symptom severity instrument (GERD-HRQL). GERD-HRQL is a validated 11-item instrument to quantify symptom severity of GERD, dysphagia, odynophagia, and gas bloat symptoms as well as patient satisfaction [26]..Additional symptoms, including regurgitation, chest pain, abdominal pain, nausea, vomiting, postprandial pain, cardiovascular, and pulmonary complaints in the 30-day postoperative period and at 1-year follow-up, will be measured by a numeric rating scale. Numeric rating scales have been used in prior outcomes research for PEHR [19, 22, 23] and measure patient symptoms experienced in the preceding 7 days.Other variables collected include postoperative wound and medical morbidity, length of stay, readmission, and patient-reported outcomes. These outcomes will be collected as standard of care in the Digestive Disease and Surgery Institute Quality Collaborative (DDSI-QC). Clavien-Dindo Classification and Comprehensive Complication Index, both validated tools [27, 28], will also be used to measure postoperative complications, morbidity and disease burden for each patient.

### Participant timeline {13}

Estimated patient accrual time is 4 years. Data collection will occur over 1 year from randomization of each patient, which includes the immediate 30-day postoperative and 1-year follow-up periods. Data analysis and manuscript production will occur within 6 months of the completion of data collection (Table 1).

**Table 1 Tab1:** Schedule of enrolment, interventions, and assessments

	Study period			
	Enrolment	Allocation	Post-allocation	Close-out
**Timepoint**	**Preoperative period**	**Intraoperative**	**30-day follow-up**	**1-year follow-up**
**ENROLMENT:**				
**Eligibility screen**	**X**			
**Informed consent**	**X**			
**Allocation**		**X**		
**INTERVENTIONS:**				
**No gastropexy**		**X**		
**Gastropexy**		**X**		
**ASSESSMENTS:**				
**PEH recurrence**				**X**
**GERD**	**X**		**X**	**X**
**Dysphagia**	**X**		**X**	**X**
**Odynophagia**	**X**		**X**	**X**
**Gas bloat**	**X**		**X**	**X**
**Regurgitation**	**X**		**X**	**X**
**Chest pain**	**X**		**X**	**X**
**Abdominal pain**	**X**		**X**	**X**
**Nausea**	**X**		**X**	**X**
**Vomiting**	**X**		**X**	**X**
**Postprandial pain**	**X**		**X**	**X**
**Cardiovascular symptoms**	**X**		**X**	**X**
**Pulmonary symptoms**	**X**		**X**	**X**
**Patient satisfaction**			**X**	**X**
**Demographic data**	**X**			
**Operative details**		**X**		
**Wound morbidity**			**X**	
**Medical morbidity**			**X**	
**Length of stay**			**X**	
**Readmission**			**X**	**X**

*PEH* paraesophageal hernia, *GERD* gastroesophageal reflux disease

### Sample size {14}

Assuming a 20% rate of loss to follow-up, enrollment of 240 participants with 120 participants in each arm will provide at least 80% power for showing superiority of anterior gastropexy to no anterior gastropexy for the primary endpoint of decreased recurrence rates by 15% at the 1-year postoperative visit using a two-sided chi-square test and an alpha level of 5%. For the purpose of calculating the power of this study, the proportion of recurrences in the control group (no anterior gastropexy) is estimated to be 0.24. This is based on the reported recurrence rates for paraesophageal hernia repair without gastropexy, ranging from 7 to 66% [3, 16, 21–24], with the majority falling between 13 and 42% [3, 16, 23, 24] at various time points after surgery.

### Recruitment {15}

CCF hospital system is a quaternary care referral center and the DDSI performs approximately 80–100 PEHR annually. An accrual time of 4 years is estimated to be adequate to recruit 240 participants. Strategies for achieving adequate participant enrollment to reach target sample size includes offering all eligible patients seen in clinic the opportunity to participate. There remains a potential to expand this study to include other minimally invasive CCF surgeons with expertise in foregut surgery if needed for patient enrollment as well.

#### Assignment of interventions: allocation

##### Sequence generation {16a}

This is a two-armed trial with an allocation ratio of 1:1 between the control (no anterior gastropexy) and intervention (anterior gastropexy) arms. Patients are randomized using a computer-generated random allocation sequence. The random allocation sequence was built using a Research Electronic Data Capture (RedCAP®) database hosted at Cleveland Clinic Main Campus in Cleveland, Ohio. A randomization allocation table has been generated and uploaded into REDCap® by a CCF statistician. No planned restrictions will be included. Both institutions involved in this study will use the same randomization allocation sequence that is hosted at Cleveland Clinic Main Campus in Cleveland, Ohio.

##### Concealment mechanism {16b}

No concealment envelope or alternative mechanism is necessary since allocation will occur in the operating room when the patient is under general anesthesia. After crural reapproximation, surgeons at either institution will ask the circulating operating room nurse to call the study coordinator and/or a research fellow hosted at the Cleveland Clinic Main Campus. The study coordinator and/or a research fellow will generate the allocation sequence at this point and inform the operating room nurse and surgeon of the result.

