### Eligibility criteria {10}

The study population includes adult patients (≥ 18 years) undergoing elective, minimally invasive repair of a symptomatic, primary paraesophageal hernia measuring at least 5 cm in height on computed tomography (CT), upper gastrointestinal series (UGI), or endoscopy, where the diaphragmatic crura can be primarily reapproximated at the time of surgery without the use of mesh using either a laparoscopic or robotic approach. Only patients who are able to participate in follow-up and consent to participate will be included. Patients whose operations begin with a minimally invasive approach and are converted to open will be included provided that they meet all other criteria. The technique for crural closure and the use or avoidance of a fundoplication are both left to the discretion of the surgeon.

Exclusion criteria include patients who are not eligible for a minimally invasive repair or have undergone prior esophageal or gastric operations, including hiatal hernia repair, cruroplasty, esophageal lengthening procedures, esophagectomy, or any prior gastric resections. However, patients who have previously undergone gastrostomy tube placement alone will remain eligible for inclusion. Additional exclusion criteria include patients undergoing PEHR with a concurrent bariatric procedure (sleeve gastrectomy, Roux-en-Y gastric bypass, duodenal switch, single-anastomosis gastric bypass, and total gastrectomy), as well as patients undergoing PEHR with concomitant placement of a gastrostomy tube. If the surgeon feels mesh is necessary to augment hiatal closure at the time of operation or if a Collis gastroplasty is required for esophageal length, these patients will also be excluded. Reasons for patient exclusions from the trial will be documented and reported in the Consort diagram.

Surgeon eligibility requires fellowship training with expertise in minimally invasive PEHR. All participating surgeons are also required to undergo training to ensure understanding of the protocol and technical aspects of performing the anterior gastropexy as described in the protocol.

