##### Implementation {16c}

The participating surgeons (PI or Co-Is) and appropriate research personnel are responsible for enrollment during the preoperative clinic evaluation. A study coordinator and/or a research fellow is responsible for generating the allocation sequence intraoperatively per surgeon request after crural reapproximation.

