##### Confidentiality {27}

Subject anonymity and data confidentiality will be maintained before, during, and after the trial period. Every effort will be made to maintain the confidentiality of documents that identify the subject by name (e.g., signed informed consent documents, clinic charts), except to the extent necessary to allow monitoring by the Office of Research Compliance at the Cleveland Clinic or by other regulatory authorities.

The information collected will be stored in the DDSI-QC, a secure institutional database that is used to track clinical outcomes in patients who undergo operations by surgeons in CCF’s DDSI. Written consent forms and data collection forms will be stored in binders, which will stay in a locked office in the Crile Building at CCF. Randomization will occur with the use of a customized REDCap®, a secure network/firewall-protected electronic database to which only the investigator and the designated members of the study team will have access using an individually assigned login and password. Only approved study members listed on the Institutional Review Board (IRB) protocol will have access to the separately stored master list—which will be stored in a Cleveland Clinic password-protected computer and saved on an S drive. Only the Principal Investigator, lead research coordinators, and biostatisticians will be granted access to retrieve patient data for data quality assessment and data analysis. All electronic records pertaining to the clinical study will be password-protected and only approved study members listed on the IRB protocol will have password access.

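### Section 16b declares allocation concealment unnecessary because the patient is anaesthetised; that is a reason for patient blinding, and the protocol also contradicts itself on when and by whom the sequence is generated

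*Protocol article*

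**What the plan says.** All references are to the protocol article.

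- **Concealment mechanism {16b}** opens with: "No concealment envelope or alternative mechanism is necessary since allocation will occur in the operating room when the patient is under general anesthesia". It then describes a call by the circulating nurse, after crural reapproximation, to a coordinator or research fellow at the main campus, who "will generate the allocation sequence at this point and inform the operating room nurse and surgeon of the result".
- **Sequence generation {16a}**: "A randomization allocation table has been generated and uploaded into REDCap® by a CCF statistician". There are no planned restrictions, and both hospitals share the one sequence.
- **Implementation {16c}**: "The participating surgeons (PI or Co-Is) and appropriate research personnel are responsible for enrollment during the preoperative clinic evaluation". It repeats that a coordinator or fellow generates the sequence during the operation.
- **Confidentiality {27}** describes the randomisation REDCap as a database "to which only the investigator and the designated members of the study team will have access using an individually assigned login and password". It does not say who can view the allocation table.
- **Eligibility criteria {10}** excludes patients on an intraoperative judgement: "If the surgeon feels mesh is necessary to augment hiatal closure at the time of operation", or if a Collis gastroplasty is required.
- **Criteria for discontinuing or modifying allocated interventions {11b}** lets the surgeon withdraw a patient at any point in the operation.
- **Strategies to improve adherence {11c}** and **Who will be blinded {17a}** rely on randomisation after crural closure to avoid or limit surgeon bias up to that step.

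**The concern.** The reason given in 16b answers a different question. Blinding concerns who knows the arm after assignment. Concealment concerns who can know the next assignment before the patient is irrevocably in the trial. An anaesthetised patient takes no entry decisions. The surgeon does, and takes them minutes before the call, on judgements about the hiatus and oesophageal length that plausibly track recurrence risk.

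If the next assignment could be learned at that moment, a patient with a poor hiatus could be steered out of the trial when a particular arm was due. That is selection before randomisation. An intention-to-treat analysis does not repair it, because the diverted patients are never in the randomised set. The statements in 11c and 17a that late randomisation guards against surgeon bias hold only if the surgeon cannot know what comes next, which is exactly what 16b says needs no mechanism.

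The contradiction about the sequence adds to this. A list fixed in advance by a statistician and a sequence produced by a team member on the telephone are different procedures with different security.

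**Working it through.** No figure in the protocol is in dispute, so the main check is a comparison of sections.

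**1. Does the stated reason support the conclusion?** Section 17a uses the same fact, general anaesthesia at allocation, to explain why patients are blinded, and there it is apt. In 16b it is the only reason given for having no concealment mechanism. It bears on neither the surgeon nor the research team. The conclusion does not follow.

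**2. Are there entry decisions that concealment must protect?** Intervention description {11a} gives the order: mobilisation, crural closure, exclusion if mesh or Collis is deemed necessary, then randomisation. The Discussion confirms that Collis patients are not randomised. Section 10 itself fixes the mesh decision only at the time of operation; that it precedes allocation follows from the order in 11a. Withdrawal under 11b may fall before or after allocation, and only the earlier part is relevant here.

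**3. Could the assignment be known beforehand?**
- *Guessing from past assignments:* no. With no restrictions and a 1:1 ratio, earlier assignments do not predict the next.
- *Seeing the list:* not stated. The list exists in advance (16a). Section 27 grants a database login to the investigator and designated team members. Under 16c the participating surgeons are the PI or Co-Is, and section 5d places surgeons and fellows in one research team that meets weekly. A login is not the same as a right to view the allocation table, and the article does not say which applies.

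**4. Who generates the sequence, and when?** Section 16a: a statistician, already done. Sections 16b and 16c: a coordinator or fellow, during the operation. These cannot both be literally true. The likely meaning is that staff retrieve the next entry from the uploaded list.

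**5. Scale.** The planned effect reproduces as a 15-point absolute difference, 0.24 against 0.09. With mean proportion 0.165, two-sided alpha 5% and 80% power, the chi-square formula without continuity correction gives

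n = [1.960·√(2·0.165·0.835) + 0.842·√(0.24·0.76 + 0.09·0.91)]² / 0.15² ≈ 95 per arm.

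Then 95/0.80 = 118.75, rounded up to 119 per arm or 238 in total, against the stated 240. Power at 96 evaluable per arm is 80.4%.

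The protocol gives nothing from which to size a selection bias. As an illustration only, *assume* that 10% of candidates have a visibly poor hiatus with 60% recurrence, within an overall control rate of 24%, and that the next assignment is fully known:
- half of them diverted from the control arm only: (0.24 − 0.05·0.60)/0.95 = 0.221, a fall of 1.9 points;
- all of them diverted: (0.24 − 0.10·0.60)/0.90 = 0.200, a fall of 4.0 points.

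Diversion from the intervention arm would bias the other way. None of these inputs comes from the documents.

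**The case against.** The strongest reply is that the process is concealed and only its justification is faulty. A statistician prepared the list, release is by telephone from a remote coordinator or fellow and only after crural closure, and simple randomisation removes prediction. User rights in REDCap are the sort of detail that a journal article leaves to the full protocol. Consent is preoperative and section 10 requires reasons for exclusion to be reported in the CONSORT diagram, so diversion would leave a trace.

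Much of this stands. A reader might infer that surgeons can see upcoming assignments. The documents do not support that: section 27 speaks of a login, under a confidentiality heading, and not of access to the table. A reader might also infer that the surgeon is unblinded throughout. Under 16b and 17a the surgeon learns the arm only after closure, and no section says that the arm is known when mesh or Collis is decided. Nor can the illustrative shift be read as an estimate: it needs full foreknowledge, which nothing documents, and even its extreme is 4.0 points against a planned 15.

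What does not stand is the appeal to condensation. The article does not merely omit a detail. It states that no mechanism is needed, for a reason that does not bear on concealment, and it gives two incompatible accounts of sequence generation. Reporting exclusions makes diversion visible afterwards but does not prevent it.

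**Conclusion.** The point holds as a flaw in what the protocol declares, not as evidence that allocation is open. The sentence in 16b is wrong in its reasoning and disclaims the safeguard on which 11c and 17a depend. Sections 16a, 16b and 16c must be reconciled on who generates the sequence and when.

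Whether allocation is concealed in practice turns on one unstated fact: whether the uploaded table is hidden from everyone who can reach the surgeon before the call. If it is, the remedy is wording. If it is not, the trial is exposed to selection before randomisation, of a size that the documents do not allow one to derive and a direction that could go either way.

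Withdrawal after allocation is a separate matter; concealment does not address it. The sample size is unaffected.

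**What to change.** In 16b:
- delete the anaesthesia rationale, which belongs only under blinding in 17a;
- name central REDCap allocation by telephone as the concealment mechanism;
- state that only the statistician who uploaded the table can view it, and that investigators, coordinators and fellows have randomise-only rights;
- state that an assignment is released only after a time-stamped confirmation that crural closure is complete and that neither mesh nor a Collis gastroplasty will be used. These are the protocol's existing entry conditions.

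In 16b and 16c, replace the wording about generating the sequence with *retrieve the next assignment*, so that both agree with 16a.

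Because the article describes recruitment as under way since June 2019, the sponsor should also record which viewing rights have applied from the start. If the table was already hidden, saying so settles the main question for the patients already randomised.

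The cost is a check or change of REDCap user rights, a short confirmation form before release, and a few sentences of text. No additional patients or staff are needed.
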